### Economic analysis

The economic evaluation will be conducted from the perspective of the health and community service provider. Data will be collected regarding costs of the exercise and home hazard reduction program delivery (including staff costs, training, capital costs and consumables). Inpatient hospital admissions and duration, emergency department presentations and other health and community service contact (including GP and specialist visits) will be recorded via the monthly calendars. Pharmaceutical use will also be collected. Incremental cost-effectiveness ratios will be calculated using multiple health outcomes, i.e. the incremental cost per a) fall prevented, b) per fall requiring medical attention avoided, c) ED presentation avoided, d) hospital admission avoided, and e) QALY gained (based on the EQ5D-5 L). Using the mean costs in each trial arm, and the mean health outcomes in each arm, the incremental cost per health outcome (a-e, above) of the intervention group compared to the control group will be calculated and results will be plotted on a cost-effectiveness plane. Bootstrapping will be used to estimate a distribution around costs and health outcomes, and to calculate the confidence intervals around the incremental cost-effectiveness ratios taking account of joint uncertainty in costs and benefits. One way sensitivity analysis will be conducted around key variables; a cost-effectiveness acceptability curve will be plotted. A cost-effectiveness acceptability curve provides information about the probability that an intervention is cost-effective, given a decision maker’s willingness to pay for each additional health outcome gained.

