### Measurement and procedures

All eligible participants will be visited at home by a research physiotherapist. The study will be explained in detail to the participant and their carer and written consent will be obtained prior to the baseline assessment. Capacity to consent will be determined by whether the potential participant demonstrates an ability to comprehend, retain and recall information about the study and any risks involved. Where there is doubt about a potential participant’s ability to process, retain and recall information about the study, assent to participate will be obtained from the identified “person responsible”.

All participants will be assessed in their home at three time points: on entry to the study (baseline assessment, prior to randomisation); at 6 months post randomisation and at 12 months post randomisation. Table 1 highlights the measures to be undertaken at each time point. Post randomisation assessments will be undertaken by assessors blinded to group allocation.

**Table 1 T1:** List of measures collected at baseline (BA), 6 month (6A), and 12 month assessments (12A) for all study participants

**Information collected for all participants**	**BA**	**6A**	**12A**	**O**

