**Quality of life**				
The EQ5D-5 L is a widely used utility-based quality of life instrument for estimating QALYs for economic evaluations [18]	Y	Y	Y	S

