### Randomisation

Participants will be randomised after completion of the baseline assessment. Randomisation will be stratified by hospital recruitment site using computer generated random numbers with variable block sizes of 6–8. The randomisation will be performed centrally using an independent web-based program by an investigator not involved in assessment or intervention.

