### Statistical methods

An intention-to-treat approach will be used for all analyses. The number of falls per person-year in the intervention and control groups will be compared with incidence rate ratios using negative binomial regression. This provides a more powerful analysis than a simple comparison of the proportion of fallers in the follow-up period, as it takes into account all falls during the trial, and also the distribution of falls, which is Poisson-like but has a longer tail. General linear models will be used to assess the effect of group allocation on the continuously scored secondary outcome measures. Modified Poisson regression models will be used to compare groups on dichotomous outcome measures. Predictors of adoption and adherence will be analysed using multivariate modelling techniques such as multiple linear and logistic regression.

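### The cost per QALY is formed from arm means with no baseline adjustment named, although EQ5D-5L utility is measured before randomisation; adjusting for it would be a free gain in precision

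*Protocol article*

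**What the plan says.** The Economic analysis section lists five health outcomes for the incremental cost-effectiveness ratios: falls, falls needing medical attention, emergency department presentations, hospital admissions and QALYs from the EQ5D-5L. One rule covers all five: "Using the mean costs in each trial arm, and the mean health outcomes in each arm, the incremental cost per health outcome" is computed for intervention against control. On uncertainty it says "Bootstrapping will be used to estimate a distribution around costs and health outcomes", followed by intervals for the ratios, one-way sensitivity analyses and an acceptability curve. No regression step and no covariate appear in that section.

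Table 1 (Quality of life) introduces the instrument with "The EQ5D-5 L is a widely used utility-based quality of life instrument for estimating QALYs for economic evaluations" and marks it for all three assessments. Measurement and procedures times these "on entry to the study (baseline assessment, prior to randomisation); at 6 months post randomisation and at 12 months post randomisation". The first EQ5D-5L value is therefore a true pre-randomisation covariate.

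Two other sections matter:
- Randomisation: "Randomisation will be stratified by hospital recruitment site using computer generated random numbers with variable block sizes of 6–8". Nothing in the design balances baseline utility.
- Statistical methods: "General linear models will be used to assess the effect of group allocation on the continuously scored secondary outcome measures". No baseline covariate is named there, and these models are not linked to the cost-effectiveness ratios.

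**The concern.** A QALY total built from utilities at 0, 6 and 12 months contains a value recorded before the programme could act. People who start with higher utility also tend to score higher later. If one arm happens to start higher, its mean QALY total will be higher for that reason alone, and a simple difference of arm means does not separate this from an effect of the programme.

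The QALY difference is the denominator of the cost-per-QALY ratio. A shift in a denominator is not damped: if the true gain is small, a modest shift can change the ratio considerably. The covariate that would remove most of this noise is already being collected.

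**Working it through.** **Plan's own figure.** The Economic analysis section gives no number to reproduce. The one planning figure used here is 180 per group, from Sample size. With control rate 1.8, IRR 0.70 (intervention rate 1.26), over-dispersion 0.8, 11 months of follow-up, 80% power and an assumed two-sided 5% level:
- V0 = (12/11)(2/1.8) + 1.6 = 2.812
- V1 = (12/11)(1/1.8 + 1/1.26) + 1.6 = 3.072
- n = (1.960√V0 + 0.842√V1)² / (ln 0.70)² = 178.2 per group

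This agrees with 180. Other variance conventions give 187.5 and 189.5 at 11 months. The point below does not depend on which was used.

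**Inputs for the QALY check**
- n = 180 per arm, complete data (Sample size; completeness is assumed)
- Utilities u0, u6 and u12 at 0, 6 and 12 months (Table 1)
- QALY rule: trapezoid over 12 months (assumed)
- Utility SD 0.20 at each visit and equal correlation r between visits, 0.5 to 0.8 (assumed; the article gives neither)

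**Step 1. Weight of baseline.** QALY = 0.25 u0 + 0.50 u6 + 0.25 u12.

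**Step 2. Size of chance imbalance.** SE of the baseline difference = 0.20 × √(2/180) = 0.0211. The 95% range is ±1.96 × 0.0211 = ±0.041.

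**Step 3. Carry-over into QALYs.** The expected shift per unit of imbalance is 0.25 + 0.75r: 0.625 at r = 0.5 and 0.85 at r = 0.8.
- Imbalance of 1 SE: 0.0211 × 0.625 = 0.013; 0.0211 × 0.85 = 0.018 QALY
- Imbalance at the 95% limit: 0.041 × 0.625 = 0.026; 0.041 × 0.85 = 0.035 QALY

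**Step 4. Precision.** The squared weights sum to 0.375, so Var(QALY) = SD²(0.375 + 0.625r). Given baseline, the residual variance is SD²[0.375 + 0.625r − (0.25 + 0.75r)²].

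| r | Variance / SD² | Residual / SD² | SE unadjusted | SE adjusted | Reduction in SE |
|---|---|---|---|---|---|
| 0.5 | 0.6875 | 0.2969 | 0.0175 | 0.0115 | 34% |
| 0.6 | 0.7500 | 0.2600 | 0.0183 | 0.0107 | 41% |
| 0.8 | 0.8750 | 0.1525 | 0.0197 | 0.0082 | 58% |

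**Step 5. Sensitivity to the assumptions.** Over SD 0.15 to 0.30 and r 0.4 to 0.8, a 1-SE imbalance shifts the QALY difference by 0.009 to 0.027. The proportional gain in precision does not depend on the SD. At r = 0.4 and SD 0.20 the SE falls from 0.0167 to 0.0120, or 28%. With 165 per arm (180 × 11/12, a rough allowance for loss), SD 0.20 and r = 0.6, the 1-SE shift is 0.0154 and the SE falls from 0.0191 to 0.0112, so the picture is the same.

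**Step 6. Effect on the ratio.** At r = 0.6 the 1-SE shift is 0.0211 × 0.70 = 0.0148. Hold the cost difference fixed. For an assumed true gain of 0.03 QALY, the ratio is multiplied by 0.03/0.0448 = 0.67 or 0.03/0.0152 = 1.97, depending on direction. For a gain of 0.05 the multipliers are 0.77 and 1.42. The article gives no expected QALY gain, so these are illustrations only.

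**The case against.** The strongest reply is that nothing here is invalid. Randomisation makes the difference of arm means unbiased, chance imbalance is ordinary sampling variation, and the planned bootstrap carries that variation into the intervals and the acceptability curve. This stands. A reader might infer that the stated rule biases the cost per QALY or miscounts QALYs as a matter of course; the document does not support that. What remains is avoidable imprecision, and a shift conditional on the imbalance that actually occurs. The bootstrap resamples around that imbalance and does not remove it.

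A second reply is that the article never says the means are unadjusted, and that an analysis plan not shown here could define model-based means. That is possible. But the article does state how the ratio is formed and goes on to the bootstrap, plane, sensitivity analysis and acceptability curve, so a difference of simple arm means is the natural reading. The point is a better choice of estimator, not a complaint about missing detail.

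Third, the area-under-the-curve rule, the SD and the correlation come from outside the document. That also stands, and every figure above is conditional on them. The 0.026 to 0.035 shift belongs to an imbalance at the edge of the 95% range and should not be read as typical.

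Finally, a reader might extend the point to costs or to the other ratios. The document does not support this. Outcome measures describes resource use recorded over the 12-month study period and no baseline cost, and baseline utility is not a component of falls, medically attended falls, emergency presentations or admissions. Nor does the article rank cost per QALY above the other four ratios.

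**Conclusion.** The point holds for the cost-per-QALY ratio only, as an improvement to a valid analysis. The stated rule leaves unused a covariate measured before randomisation. Under the base assumptions set out above, a chance imbalance of ordinary size is enough to move the QALY difference by an amount comparable with its own adjusted standard error, and the achievable gain in precision is worth having. The direction of the argument is secure if QALYs use the area under the curve and utilities correlate positively within person; the exact size is not. The primary falls analysis is untouched.

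**What to change.** Reword the Economic analysis section, or state in the analysis plan before unblinded data are seen, that:
- QALYs are calculated by a named rule from the utilities at 0, 6 and 12 months;
- incremental QALYs are the group coefficient from a regression with baseline EQ5D-5L utility and recruitment site as covariates;
- this model is refitted within each bootstrap resample together with the cost difference from the same resampled participants, so that the correlation between costs and QALYs is kept;
- the adjusted QALY increment is used in the cost-per-QALY ratio, its plane and its acceptability curve;
- the unadjusted arm means are reported as a sensitivity analysis.

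The cost is wording and a little programming. No new data, visits or participants are needed, because the baseline EQ5D-5L is already in Table 1.

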## Discussion

Cognitive impairment (including dementia) is a national and international health priority and the challenges faced with managing the increasing incidence and prevalence of this syndrome are substantial for individuals, health care systems and society more generally. Failing to address the issue of falls and fall related injury in this group has enormous consequences with huge cost implications to both the health and aged care sectors as well as to families and the informal care network more broadly.

Most older people, including those with CI, wish to remain in their own home for as long as possible. By reducing the rate of falls and fall related injury we anticipate preventing functional decline as well as reducing fall-related hospitalisations and the need for escalation in care including a move to a residential aged care facility.

This study will build on extensive pilot work that has identified important risk factors for falls amenable to intervention in older people with CI [1,11-13]. If found to be efficacious in preventing falls, we anticipate the findings will contribute to future guidelines and policies and improve clinical services and the care required for the increasing number of older people with CI across the world.

## Abbreviations

CI: Cognitive impairment; MMSE: Mini-mental state examination; ACE-III: Addenbrookes cognitive examination; FES-I: Falls efficacy scale; IPEQ: The incidental and planned exercise questionnaire; QALYs: Quality adjusted life-years; EQ5D-5 L: EuroQoL 5 dimensions 5-levels; MoCA: The montreal cognitive assessment.
